### Assignment of interventions: allocation

#### Sequence generation {16a}

Randomisation allocations were generated by an automated web/telephone randomisation system provided by the Bristol Trials Centre until November 2023, and subsequently by an online randomisation system called Sealed Envelope™. The randomisation system is stratified by site and minimised by age (65–79 vs 80 and over).

#### Concealment mechanism {16b}

The web-based and telephone randomisation systems ensure allocation concealment. Minimisation with probability weighting of 0.8 is used in order to reduce predictability. Participants are randomised once written consent has been provided and all baseline measurements completed.

#### Implementation {16c}

GCP-trained doctors, research nurses or delegated team members at the site enrol patients and use the automated randomisation system to assign the participants to the interventions. All patients that enter the study are given a unique, six-digit study (participant) identification number generated by the randomisation system.

### Assignment of interventions: Blinding

#### Who will be blinded {17a}

Due to the nature of the intervention, participants and those administering the intervention are not blinded to group allocation. Patients are, however, blinded to their randomised allocation prior to completion of their baseline questionnaire to remove bias. Two statisticians are supporting the trial. The senior statistician will remain blinded throughout the trial and be responsible for writing the statistical analysis plan (SAP) and attending TSC meetings. The other trial statistician will perform all disaggregated analyses according to a pre-specified statistical analysis plan and will attend closed Data Monitoring Committee (DMC) meetings, as required. The remaining members of the study team will remain blinded to aggregate data only.

#### Procedure for unblinding if needed {17b}

There is no requirement for unblinding.

### Data collection and management

#### Plans for assessment and collection of outcomes {18a}

##### Baseline assessment and data collection for the RCT

Following consent and prior to randomisation, participants complete a patient questionnaire and demographic, social, clinical, resource use and laboratory data (Table 1) are collected. The physical assessment is carried out by the research nurse following standard operating procedures. No additional blood or urine tests are required other than those already performed as part of routine care.

**Table 1 Tab1:** Summary of baseline data collection for the RCT

Demographics/social	Age, sex, ethnicity, marital status, education level, distance lived from kidney clinic, alcohol consumption, smoking history
Clinical	Primary kidney disease, date first seen by nephrologist, comorbidities, dietary restrictions, prescribed medication
Resource use	Hospital/nursing home/residential home days/hospice days, other hospital outpatient services and primary care and community services in the last 4 months. Help from family, friends and carers in the last week
Laboratory	Creatinine, urea, albumin, haemoglobin, haematocrit, mean corpuscular volume, sodium, potassium, bicarbonate, corrected calcium, phosphate, intact parathyroid hormone, total cholesterol. (From the date of the study visit or the closest date prior to the study visit.)
Physical assessment	Height, weight, blood pressure, heart rate, waist circumference, timed get up and go [30], hand grip strength (Jamar hand dynamometer) [31], WHO performance status
Patient reported	EQ-5D-5L [25], IPOS-renal [26], ICECAP-O [27], ICECAP-SCM [28], MTBQ [29]
Relative/carer reported	PACKS impact on carers questionnaire [32]

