Based on summary statistics from the observed data and visual inspection of the histogram, we simulated datasets of 1,000,000 observations for comparator groups using the SKBIM command in STATA [40]. This command allows the user to simulate a bimodal distribution while specifying different characteristics of the distribution including means, standard deviations, skewness and kurtosis (for the comparator group the simulated dataset was generated with this command: skbim (0.5 0.359 0.096 2.413 2.413 0.154 1 1000000 123 0.804 2.492 0 3)). To simulate the distribution of QALYs in the intervention group, we assumed the same distribution as the comparator group, but shifted the two means by 0.345 QALYs to reflect a clinically meaningful difference we wanted to be able to detect. Simulated values greater than 3 were discarded.

Sample size calculations involved re-sampling (1000 iterations) with varying sample sizes from these simulated distributions of continuous QALY scores and performing Mann Whitney tests. To allow for possible cross over, we selected our intervention group samples by taking 95% of our sample from the intervention distribution and 5% from the comparator distribution. The same process was used to identify the comparator group sample.

Having 230 patients per group allows detection of a difference between the pathways of 0.345 QALYs with 90% power (2-sided a = 0.05). Death is not a censoring event (utility becomes and remains 0) so loss-to-follow-up should not exceed 10%. Allowing for loss-to-follow-up increased the total sample size to 512.

Following the COVID-19 pandemic, recruitment rates have improved but are still generally tracking below predicted. Following discussions with the Trial Steering Committee (TSC), Patient Advisory Group (PAG) and funder, the Trial Management Group (TMG) has agreed to extend recruitment to ensure 85% power is achieved. Using the original sample size simulations and associated assumptions, this reduces the target sample size from 512 to 446 participants.

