## Statistical methods

### Statistical methods for primary and secondary outcomes {20a}

All data analysis will be in accordance with the Consolidating Standards of Reporting Trials (CONSORT) [48, 49] guidelines and the primary statistical analyses will be conducted on a modified intention-to-treat basis including all participants contributing at least one quality of life measurement. Baseline variables to be explored are shown (Table 1). Patient-reported outcome scores based on standardised questionnaires will be calculated based on the developers’ scoring manuals and missing and erroneous items will be handled according to these manuals. Continuous measures will be presented as means and standard deviations or medians and ranges depending on their distribution. Categorical data will be presented as frequencies and proportions. A full statistical analysis plan will be developed and agreed by the Trial Steering Committee (TSC) prior to undertaking any analyses of the trial data.

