#### Primary outcome analysis

The primary endpoint in this study is quality-adjusted life years which will be calculated using EQ-5D-5L data collected 4-monthly and survival data. The primary statistical analyses between the randomised groups will be conducted on a modified intention-to-treat basis including all participants contributing at least one quality of life measurement. Utility scores will be estimated from the EQ-5D-5L using the NICE-recommended approach at the time of analysis and these will be used to compute QALYs experienced over the follow-up period using the area under the curve approach. Depending on the distribution of the observed QALYs data, appropriate regression techniques will be applied. If normally distributed, the mean differences in QALYs between treatment arms with 95% confidence intervals will be calculated using multivariate linear regression models. Otherwise, the shape of the distribution will be considered to inform the choice of alternative, suitable regression models (including non-parametric models) for this outcome. All models will adjust for baseline EQ-5D-5L scores.

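### The primary QALY model names baseline EQ-5D-5L as its only covariate; pre-specifying performance status and comorbidity score as well would give a modest, cheap gain in precision

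*Protocol article*

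**What the plan says.** The section on primary outcome analysis sets one covariate: "All models will adjust for baseline EQ-5D-5L scores". It leaves the type of model open: "Depending on the distribution of the observed QALYs data, appropriate regression techniques will be applied". If QALYs are normally distributed, the mean difference "will be calculated using multivariate linear regression models"; otherwise another model, possibly non-parametric, is chosen from the shape of the distribution. No full list of covariates is given.

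Table 1, under baseline assessment, lists the physical measures "timed get up and go [30], hand grip strength (Jamar hand dynamometer) [31], WHO performance status", comorbidities, and laboratory values beginning "Creatinine, urea, albumin, haemoglobin, haematocrit". Item 20a gives these variables no role in the model: "Baseline variables to be explored are shown (Table 1"). The same paragraph defers detail: "A full statistical analysis plan will be developed and agreed by the Trial Steering Committee (TSC) prior to undertaking any analyses of the trial data".

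Three other places bear on the point:

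- The primary outcome definition sets utility to 0 after death.
- The inclusion criteria and the subgroup section (item 20b) both use WHO performance status (cut at 3) and a comorbidity score (cut at 2). The subgroup use is within those aged 80 and over.
- Item 16a stratifies randomisation by site and minimises by age group. Neither performance status nor comorbidity is balanced by design.

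**The concern.** Total QALYs combine how well people feel with how long they live. The background section cites registry 3-year survival on dialysis of 55% at ages 65–74 and 40% at 75 and over. If trial mortality is anywhere near that, survival time will account for a large part of the spread in QALYs over about 3 years. Baseline EQ-5D-5L speaks directly to the quality part and only indirectly to the length part. Performance status and comorbidity plausibly carry further information on survival, and the trial already treats them as markers of frailty and multimorbidity.

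Variation that a baseline variable could explain but the model ignores stays in the residual and widens the interval for the QALY difference. A chance imbalance in that variable also goes uncorrected, except for the part it shares with EQ-5D-5L. What is at stake is the width of the primary confidence interval, not bias.

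**Working it through.** **1. The plan's own figures.** Inputs from the sample size section: target difference 0.345 QALYs; two-sided 5%; 5% crossover in each arm; 10% loss; two components with means 0.359 and 2.413. I read 0.5 as the mixing weight and 0.096 and 0.154 as the SDs. That reading of the simulation command is an assumption.

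- Diluted difference: 0.345 × (0.95 − 0.05) = 0.3105.
- SD of the mixture: √[0.5 × (0.096² + 0.154²) + 0.25 × (2.413 − 0.359)²] = 1.035.
- n per arm = 2 × SD² × (z₁₋α/₂ + z_power)² / d².
- 90% power: 2 × 1.035² × (1.960 + 1.282)² / 0.3105² gives 234 per arm; 468/0.9 = 520 in total, against 512 stated.
- 85% power: 2 × 1.035² × (1.960 + 1.036)² / 0.3105² gives 200 per arm; 400/0.9 gives 445 in total, against 446 stated.
- Loss allowance: 460/0.9 = 511.1, which becomes 512 as stated.

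The agreement is close but rests on a normal approximation. The plan used Mann-Whitney tests on a skewed bimodal simulation whose arguments are not fully explained. Simple normal-mixture readings of the command gave Mann-Whitney power anywhere from about 0.41 to 1.0 at 230 per arm. The plan's simulation takes no credit for any covariate, not even baseline EQ-5D-5L.

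**2. What extra covariates would add.** Let R² be the share of residual variance, after adjustment for baseline EQ-5D-5L, that the added covariates explain. In a linear model:

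- equivalent sample size = 446 / (1 − R²);
- power = Φ[(1.960 + 1.036)/√(1 − R²) − 1.960], taking the stated 85% as the benchmark for the EQ-5D-5L-only model;
- relative width of the confidence interval = √(1 − R²).

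| R² (assumed) | Equivalent N | Power | Interval width |
|---|---|---|---|
| 0.00 | 446 | 85.0% | 1.00 |
| 0.03 | 460 | 86.0% | 0.98 |
| 0.05 | 469 | 86.7% | 0.97 |
| 0.10 | 496 | 88.5% | 0.95 |
| 0.15 | 525 | 90.1% | 0.92 |
| 0.17 | 537 | 90.8% | 0.91 |

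Matching the precision of 512 participants would need R² = 1 − 446/512 = 0.129. Moving from 85% to 90% power by formula would need 1 − [(1.960 + 1.036)/(1.960 + 1.282)]² ≈ 0.146.

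**3. Where the range for R² comes from.** The documents give no R², C-index or correlation for any baseline measure. The range is therefore simulated under assumptions: Weibull survival with shape 1.2, median survival 2.0 to 3.2 years, a prognostic score with C-index 0.61 to 0.69, and QALYs equal to utility times survival capped at 3 years. If the score is unrelated to baseline utility, R² is about 0.05 to 0.22. With a correlation of 0.5 between them it falls to about 0.03 to 0.17. Overlap is likely, because EQ-5D-5L is itself a measure of health status, so the lower range is the one to use.

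**The case against.** The strongest objection is that this is not an error in the protocol. The covariate sentence sets a minimum, not a closed list, and the rest is deferred to a statistical analysis plan that is not shown. That plan may already include these variables. This stands: it would be wrong to say that the protocol excludes them.

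A reader might also infer that the trial loses stated power through the omission, or that the omission compounds the decision that "this reduces the target sample size from 512 to 446 participants". The documents support neither. The 90% and 85% figures come from unadjusted simulations and would be the same whatever the covariate list. The reduction followed slow recruitment.

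Nor do the documents show that these variables are strongly prognostic. Eligibility narrows their range: everyone has eGFR below 15, those aged 65–79 must meet the performance status or comorbidity criterion, and people not fit for dialysis are excluded. At the low end the gain is about one percentage point of power.

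The (1 − R²) arithmetic belongs to a linear model. The sample size section reports a bimodal QALY distribution in the planning data, and the primary analysis may turn out non-parametric; the gain does not carry over directly to that case.

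What the objection does not remove is the improvement itself. The protocol states a covariate rule, the data are already collected before randomisation, and under a linear model adjustment leaves the mean difference essentially unbiased while narrowing its interval.

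**Conclusion.** The point holds as a modest, low-cost improvement to a stated method, not as a defect that invalidates anything. Baseline EQ-5D-5L is the only covariate named for the primary QALY model, others are not ruled out, and two variables that the trial already relies on have no stated role. In a linear model, an assumed R² of 3% to 17% makes 446 participants worth about 460 to 537, with power of about 86% to 91% against the 85% benchmark and an interval about 2% to 9% narrower. This rests on the assumed survival pattern, C-index and overlap with EQ-5D-5L, none of which the documents give. Recovery of the full 512-participant precision lies towards the favourable end of the range and should not be counted on.

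**What to change.** Before any comparison of outcomes by arm, state in the statistical analysis plan that the primary QALY model adjusts for:

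- baseline EQ-5D-5L;
- WHO performance status, kept as an ordinal score and not dichotomised, since a cut at 3 would discard part of the information sought;
- comorbidity score;
- the randomisation factors, site and age group.

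Baseline eGFR may be added, as it can be derived from entry data; albumin only if it is nearly complete. State how missing baseline values are handled. Keep the mean QALY difference as the reported effect and the EQ-5D-5L-only model as a sensitivity analysis. If a non-parametric model remains possible, say how the same covariates enter it. If the analysis plan already lists these covariates, only the protocol wording needs aligning.

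The cost is wording, a few model degrees of freedom for the prognostic covariates (more for site, depending on how it is modelled) and simple handling of missing baseline values. No new data are needed. Fixing the list in advance also prevents the variables marked for exploration from being chosen after results are seen.

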##### Follow-up assessment and data collection for the RCT

Follow-up data collection for the RCT is summarised in Table 2. Clinical, resource use, laboratory and compliance with the intervention is collected by research nurses from primary and secondary care clinical notes and during study visits/contacts. The physical assessment is performed by the research nurse following standard operating procedures. No blood or urine tests are required other than those that will already have been performed as part of routine care.

**Table 2 Tab2:** Summary of follow up data collection for the RCT

Clinical	Co-morbidities, hospital admissions including dates and causes, dialysis access surgery procedures and complications, other surgery, dialysis treatment received, dietary restrictions, prescribed medication, date, location and cause of death
Resource use	Hospital/nursing home/residential home days/hospice days, other hospital outpatient services and primary care and community services in the last 4 months. Help from family, friends and carers in the last week
Laboratory	Creatinine, urea (pre- and post-dialysis if on haemodialysis), albumin, haemoglobin, haematocrit, mean corpuscular volume, sodium, potassium, bicarbonate, corrected calcium, phosphate, intact parathyroid hormone, total cholesterol. (From the date of the study visit/contact or the closest date prior to the study visit/contact.)
Physical assessment	Weight, blood pressure, heart rate, waist circumference, timed get up and go [30], hand grip strength (Jamar hand dynamometer) [31], WHO performance status
Compliance with trial	Number of home visits by clinical team from kidney unit; Number of attendances at CKD clinic; Number of telephone contacts from clinical team at kidney unit; Number of visits from the palliative care team; Number of telephone contacts from the palliative care team; Advance care agreed; Advance care plan reviewed/updated; Cardiopulmonary resuscitation decision documented; Preferred place of death documented
Patient reported	EQ-5D-5L [25], IPOS-renal [26], ICECAP-O [27], ICECAP-SCM [28], MTBQ [29]
Relative/carer reported	PACKS impact on carers questionnaire [32], QUALYCARE post-bereavement survey [33]

Study visits/contacts are 4-monthly (+ / − 4 weeks) until withdrawal from the study, death or end of follow-up. They are arranged face-to-face once a year (at home or in clinic) and by telephone twice a year. Patient- and carer-reported outcomes are collected via postal or electronic questionnaires every 4 months, with carers also being asked to complete a proxy-report for the deceased’s quality of life in the last week of life.

##### Data linkage

At the point of consenting to take part in the RCT or the RFU, all participants are asked to consent to linkage to existing healthcare databases, such as Hospital Episode Statistics, the Office for National Statistics, and the UK Renal Registry, and their equivalents in devolved nations. This will provide data on dates and causes for all hospital admissions, date and cause of death, and dates and modalities of acute or chronic dialysis, if initiated. This will enable follow-up of outcomes (though not quality of life) for participants who wish to stop providing data to the study who might otherwise be lost to follow-up, including those who move to a kidney unit not participating in the trial.

##### Resource-use data collection

Data is collected as detailed in trial assessments and data collection. Costs from the NHS and PSS perspective will include costs associated with hospital, hospice and general practice and community care, and will include the costs of facilities, staff salaries and medication. For both interventions, appropriate preparation costs will be included, as will costs associated with delivery of the pathway of care experienced by the patient. Discussion with clinical collaborators prior to the start of the trial ensured that all relevant resource use is captured. For participants preparing for the responsive management pathway, this is likely to include additional support for the patient and their family/friends/carer, as well as routine monitoring. For participants preparing for dialysis, this will include all visits, scans, surgical appointments and surgical/radiological procedures. Where possible, resource-use data will be obtained routinely, through routine hospital data (e.g. hospital episode statistics), as such data are generally more comprehensive. Resource use that is not captured through routine sources is captured through the clinical trial documentation or questionnaires (adapted version of the Client Service Receipt Inventory) administered to patients and their family/friend/carer at follow-up as appropriate.

#### Plans to promote participant retention and complete follow-up {18b}

For patient-reported outcomes, up to three reminders are conducted. If a patient becomes too unwell to complete the patient questionnaires, a proxy report from a relative/carer is accepted. Patients who discontinue allocated treatment can choose to continue to receive patient questionnaires, attend follow-up contacts and allow data linkage.

#### Data management {19}

All data held in Bristol conforms to the University of Bristol Data Security Policy and is in compliance with the General Data Protection Regulation and the Data Protection Act 2018. Study data is collected and managed using REDCap [47] hosted at the University of Bristol. The database incorporates data entry and validation rules to reduce data entry errors, and management functions to facilitate auditing and data quality assurance.

Data collected on the paper CRFs at study centres, or as questionnaires from participants, is identifiable only by participant study number. Information capable of identifying individuals and the nature of treatment received is held in the database with restricted access to Prepare for Kidney Care study staff and essential national database staff. Some participants complete questionnaires online, and in such cases, these are completed directly onto a secure web-based database by the participants. Paperwork is transferred to the central study office via secure email or tamperproof envelopes and via recorded delivery.

Identifiable information, as agreed with partner organisations and set out in the participant information sheet, is used to link this primary dataset with existing routine healthcare databases for follow-up. The database system protects patient information in line with the data protection legislation and any specific requirements of the partner organisations. Trial and database staff ensure that participants’ anonymity is maintained through protective and secure handling and storage of patient information. The chief investigator acts as custodian of the full dataset.

##### Retention of data

Completed case report forms will be kept for 5 years following the end of the study to enable audit of data used in publications. These will be kept at the UoB for this time and then destroyed.

#### Confidentiality {27}

Personal identifiable and clinical data will be processed in compliance with the Common Law Duty of Confidentiality and Data Protection Act 2018, as set out in the privacy notice on the trial website [21].

